## Abstract

**Objective:**

To describe the protocol of a prospective study to test the validity of intermuscular coherence (IMC) as a diagnostic tool and biomarker of upper motor neuron degeneration in amyotrophic lateral sclerosis (ALS).

**Methods:**

This is a multicenter, prospective study. IMC of muscle pairs in the upper and lower limbs is gathered in ∼650 subjects across three groups using surface electrodes and conventional electromyography (EMG) machines. The following subjects will be tested: 1) neurotypical controls; 2) patients with symptomatology suggestive for early ALS but not meeting probable or definite ALS by Awaji Criteria; 3) patients with a known ALS mimic. The recruitment period is between 3/31/2021 and 12/31/2025. Written consent will be sought from the subject or the subject’s legally authorized representative during enrollment.

**Results:**

The endpoints of this study include: 1) whether adding IMC to the Awaji ALS criteria improve its sensitivity in early ALS and can allow for diagnosis earlier; 2) constructing a database of IMC across different ages, genders, and ethnicities.

**Significance:**

This study may validate a new inexpensive, painless, and widely available tool for the diagnosis of ALS.

## Introduction

Amyotrophic lateral sclerosis (ALS) is a progressive, uniformly fatal neurodegenerative disorder characterized by the loss of motor neurons in the brain and spinal cord. The loss of motor neurons results in paralysis and death, typically within 5 years and with 60% mortality by 3 years [1, 2]. ALS is characterized by significant phenotypic, genetic, and pathogenic heterogeneity. Phenotypic variability arises in the extent and location of upper motor neuron (UMN) or lower motor neuron (LMN) involvement, with typical ALS patients having a combination of both UMN and LMN symptomatology [1, 3].

On average, there is a delay of 12–16 months from the onset of symptoms to the diagnosis of ALS [4–6]. Currently, diagnosis of ALS is based on a history of progressive weakness, exam findings of LMN and UMN dysfunction, and exclusion of diseases that mimic ALS [7, 8]. One common reason for diagnostic uncertainty and delay in diagnosis is the lack of UMN features on physical exam, as UMN signs are not always present in early ALS [9, 10]. Needle EMG features of acute and chronic denervation were set equivalent to physical exam findings of LMN dysfunction in Awaji criteria to improve the diagnostic sensitivity [8]. While needle EMG is a reliable and widely available tool to confirm LMN degeneration, physical exam is the only practical way to assess UMN loss at the present time. An objective, widely available, electrophysiological assessment of UMN dysfunction is missing from current ALS diagnostic criteria.

Intermuscular coherence (IMC) has been proposed as a marker of UMN dysfunction and preliminary reports suggest it can differentiate patients with motor neuron disease from neurotypical subjects [11–13]. The output from the motor cortex is in part oscillatory, so a portion of the activity in separate muscles involved in a motor task oscillates at the same frequency [14, 15]. As a result, the cortical signal to muscles can be assessed by measuring the coherence between two co-activated muscles (IMC) [14–21]. IMC is a method for imputing the extent of central (UMN) drive to muscles and is calculated from the patterns of surface EMG activity in muscle pairs, which is independent of EMG assessments of LMN dysfunction like interference pattern and motor unit action potential sorting and analysis [20, 22]. We here outline the protocol for Intermuscular Coherence as a Biomarker for ALS (ALS-IMC) (NCT05104710), a prospective study to validate IMC as a diagnostic tool for assessing UMN dysfunction in ALS.

Several considerations affected the development of the protocol. First, the diagnostic dilemma with ALS is usually not, whether an abnormality exists, rather whether the etiology of the abnormality is ALS or a disorder that mimics ALS. To evaluate whether IMC can distinguish between subjects with ALS and an ALS-mimic requires multiple comparator groups, including patients with ALS and patients with a variety of ALS-mimics. This is particularly useful in attempting to differentiate patients with ALS from those with lower-motor neuron mimics. Second, because IMC profiles vary based on muscles assessed, the task performed during measurement, and potentially by subject demographics, a distribution of test-specific IMC profiles must be generated in neurotypical subjects. Finally, the ideal diagnostic test would reduce the time to a definitive diagnosis, so the protocol was designed to assess whether IMC could provide a diagnosis at an earlier time point than is currently the typical.

## Materials and methods

### Study outline

The study is organized into two sections. The first establishes the distribution of test-specific IMC profiles in neurotypical subjects across demographic groups (Neurotypical IMC distributions). The second (IMC in ALS and ALS mimics) asks 1) whether adding abnormal IMC values to the Awaji criteria results in ALS diagnosis earlier in the course of disease, and 2) whether IMC is a valid tool to distinguish ALS from different ALS mimics. Written consent will be sought from the subject or the subject’s legally authorized representative during enrollment.

### Study subjects

In Aim 1, IMC distributions will be assessed in neurotypical subjects who report no current neurological issues. Subjects will be recruited to sample demographic variables including age, sex, race, and ethnicity. Measurements will be made in subjects from each decade between 20 and 80 years old, for male or female sex, African-American or White race, or Hispanic or non-Hispanic ethnicity. Depending on the overlap in ethnic and racial distributions, we anticipate that data from 240 subjects will be needed to sample the demographic space and determine how IMC varies across the neurotypical population. A measurement of IMC in both arms and both legs will be made.

In Aim 2, IMC profiles will be collected from 410 subjects (N selected based on power analysis described below) who present with symptoms suggestive for ALS but not meeting probable or definitive ALS classification using Awaji Criteria, i.e. patients with uncategorized or possible ALS according to the Awaji Criteria. Patients diagnosed with various mimic disorders will also be included. The specific inclusion and exclusion criteria are as follows:

**Inclusion:** a) Patients who present to one of the sites for upper or lower limb weakness, spastic gait, muscle wasting and/or fasciculations, dysphagia, dysarthria, shortness of breath, hyperreflexia or pathological reflexes, or findings of muscle denervation in previous EMG studies. b) Patients with a LMN mimic disease such as spinal muscular atrophy, spinal-bulbar muscular atrophy (Kennedy’s disease), multifocal motor neuropathy and other motor predominant neuropathy or radiculopathy, inclusion body myositis, other myopathies and neuromuscular junction disorders. c) Patients with an UMN mimic disease, such as primary lateral sclerosis (PLS), hereditary spastic paraparesis, ischemic or demyelinating disease with purely motor symptomatology.

**Exclusion:** a) Patients who are classified as probable or definite ALS by Awaji criteria prior to initial study evaluation, b) significant sensory loss in the weak or spastic limbs, c) significant musculoskeletal or neuropathic pain, d) inability or unwillingness to provide informed consent, e) inability to perform the study-related task, and f) subjects who have taken a GABA agonist (e.g. baclofen or benzodiazepines) within 24 hours of the study procedure.

To characterize disease state at the time of testing, information will be collected through chart review and subject interviews, including: a) date and site of onset of symptoms, b) height and weight, c) diagnostic category based on Awaji criteria, c) topographical location and pattern of UMN and LMN symptoms at the time of the IMC test.

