### Assessment of final diagnosis

A diagnosis of ALS or non-ALS condition will be made by the treating team and reviewed by a standing committee of neuromuscular specialists. Disagreement in diagnosis will be resolved by consensus; if a consensus cannot be reached the subject will be excluded from analysis. The clinical review committee will be blind to the IMC results and provisional diagnoses.

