### Sample size justification

The sample size of the study was selected to determine whether IMC can materially reduce the number of false negatives (i.e., improve sensitivity) associated with the Awaji Criteria. The initial visit Awaji criteria have a sensitivity of 56–61% (probable or definite at initial visit with eventual diagnosis of ALS) [25, 26]. We will therefore target a true change in sensitivity (*Δsens*) of 9% and will test against the null hypothesis of *Δsens* of 4% (insufficient improvement). Power analysis suggests a total of 243 cases with a final diagnosis of ALS will be needed for an α < 0.05 and a power of > 90%. To estimate the number of patients that need to be screened we assume the distribution of patients enrolled is similar to that reported by Geevasinga et al [26] in which ∼60% of patients with “possible ALS” or “uncategorized” by the Awaji criteria at first visit were eventually diagnosed with ALS, and ∼40% were diagnosed with an ALS mimic. Therefore, the total sample size required is 243/0.6 = 405. We will enroll 410 patients, which will provide ∼160 patients for estimating the change in specificity.

To determine the magnitude of diagnostic time reduction that could be detected with this sample size, a power analysis was performed. We assume a possible reduction in time-to-diagnosis of 0 to 5 months, with a uniform distribution and standard deviation of 1.4 months. An N of 243 cases of ALS would provide 90% power, at α = 0.05, to detect a true reduction in time-to-diagnosis of 0.3 months.

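### The 60% ALS yield behind the 410 holds only for undiagnosed presenters, yet patients with an established mimic appear to be counted in the 410 and pooled into the specificity and accuracy estimates, with no number or cap

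*Protocol article*

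**What the plan says.** The Abstract (Methods) describes about 650 "subjects across three groups using surface electrodes and conventional electromyography (EMG) machines". Early suspected ALS and "patients with a known ALS mimic" are listed there as two separate groups, next to neurotypical controls.

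Study subjects gives the numbers. For Aim 1, "we anticipate that data from 240 subjects will be needed to sample the demographic space". For Aim 2, "IMC profiles will be collected from 410 subjects (N selected based on power analysis described below"), described as presenters who are possible or uncategorized under Awaji. The section then adds: "Patients diagnosed with various mimic disorders will also be included". Two inclusion routes serve these patients: route (b), which begins "Patients with a LMN mimic disease such as spinal muscular atrophy, spinal-bulbar muscular atrophy (Kennedy’s disease), multifocal motor neuropathy", and route (c) for UMN mimics. Neither has a target number or a cap.

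The Sample size justification takes 243 ALS cases (change in sensitivity of 9% against a null of 4%, α of 0.05, power above 90%). It cites a 60/40 split between ALS and mimics among patients possible or uncategorized at first visit, and concludes: "Therefore, the total sample size required is 243/0.6 = 405". It enrols 410 and expects about 160 patients for the change in specificity.

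Statistical analysis estimates the change in sensitivity as c/(a+c+d), in specificity as −g/(e+g+h) and in accuracy as (c − g)/n. All patients without a final ALS diagnosis are pooled in e+g+h, and everyone is in n.

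**The concern.** The 40% in the cited split are patients who were diagnostically open at first visit and later proved to have a mimic. A patient who enters with an established mimic diagnosis comes from a different population and is not expected to become an ALS case. If such patients take places in the 410, the 60% yield no longer applies to the whole 410.

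Two things are at stake. One is the number of ALS cases, and with it the power for the sensitivity comparison. The other is what the specificity and accuracy changes mean. The test is meant for patients whose diagnosis is open. Statistical analysis frames the central question as sensitivity gained against specificity lost. If the loss is averaged over undiagnosed presenters and known mimics in proportions that nobody has set, half of that trade-off depends on recruitment.

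**Working it through.** **The plan's own figures.** 243/0.6 = 405. At 410 enrolled, 0.6 × 410 = 246 ALS cases and 0.4 × 410 = 164 others, matching the stated figure of about 160. An exact one-sided binomial test of 4% against 9% at α = 0.05 has 92.9% power with 243 cases, in line with the stated power above 90%. The protocol does not give the sidedness of this test. These figures are consistent if all 410 are possible or uncategorized presenters.

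**Where the known mimics sit.** 240 + 410 = 650, the approximate total for all three groups. That leaves no separate allocation for known mimics.

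**Effect on the case count.** Let k be the number of known mimics among the 410. Their share is not in the protocol, so 10, 20 and 30% are assumptions.

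- Expected ALS cases = 0.6 × (410 − k). At k = 5 this is 0.6 × 405 = 243; any larger k gives fewer.
- Non-ALS patients = 410 − 0.6 × (410 − k).
- Share of known mimics among the non-ALS patients: f = k / [410 − 0.6 × (410 − k)].
- Total needed to keep 243 expected cases = 405 + k.
- Power is that of the exact one-sided test, averaged over a Binomial(410 − k, 0.6) number of ALS cases.

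| Assumed share | k | Expected ALS | Non-ALS | f | Power | Total to keep 243 |
|---|---|---|---|---|---|---|
| 0% | 0 | 246 | 164 | 0% | 93.1% | 405 |
| 10% | 41 | 221 | 189 | 22% | 90.6% | 446 |
| 20% | 82 | 197 | 213 | 38% | 87.5% | 487 |
| 30% | 123 | 172 | 238 | 52% | 83.5% | 528 |

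**Effect on specificity.** The pooled loss is L × (1 − f) + M × f, where L is the loss in undiagnosed presenters and M the loss in known mimics. Neither is in the protocol. For illustration take L = 10 points:

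- M = 0 (known mimics never reclassified): pooled loss 7.8, 6.2 and 4.8 points at shares of 10, 20 and 30%.
- M = 15 points: pooled loss 10 + 5f = 11.1, 11.9 and 12.6 points.

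The same performance in presenters thus gives a pooled loss anywhere from 4.8 to 12.6 points across these assumptions.

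**Effect on accuracy.** With the planned 9% sensitivity gain and L = 10 points, presenters alone give 0.6 × 0.09 − 0.4 × 0.10 = +1.4 points whatever k is. Pooled over 410 at a 20% share, c = 0.09 × 196.8 = 17.7 and g among presenters = 0.10 × 131.2 = 13.1.

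- M = 0: (17.7 − 13.1)/410 = +1.1 points.
- M = 15 points: (17.7 − 13.1 − 0.15 × 82)/410 = −1.9 points.

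On these illustrative values even the sign depends on the mix.

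**What is not affected.** The sensitivity estimator uses only final ALS cases. Known mimics do not bias it; they only make its denominator smaller.

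**The case against.** **Known mimics may be extra, or may be part of the 40%.** The word also in Study subjects can be read as patients on top of the 410, and about 650 is approximate. Alternatively, the 60/40 split may be the mix intended for everyone enrolled. Neither reading can be excluded. But the first leaves the 650 total with no allowance for a third group, and the second needs a cap on known mimics that is not stated. Both need a correction to the text.

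**Recruiting mimics is deliberate.** Study outline asks whether IMC separates ALS from different mimics, and the Discussion plans to look at LMN and UMN mimics. This stands: enrolling them is sound. The problem is counting them toward 405/410 and pooling them in the estimators.

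**Stronger readings that a reader might infer, and that the protocol does not support:**

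- *The 243 cases and the power above 90% are definitely not delivered.* The shortfall depends on k, which is not given. At a 10% share, one-sided power is still about 91%. The chance of reaching 243 cases is not a power measure, and nothing breaks sharply at 243.
- *The lack of an attrition allowance is a defect.* Patients without a consensus diagnosis are dropped ("if a consensus cannot be reached the subject will be excluded from analysis"). But with an assumed 5% lost (390 left, no known mimics) averaged power is 92.0%, and such an allowance is commonly left to the full protocol.
- *Specificity is bound to look better than it is, because UMN mimics are true negatives by construction.* That rests on Awaji category rules that the article does not set out. The Discussion expects IMC not to separate ALS from UMN disorders, which could push the pooled loss the other way.

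**Conclusion.** The point holds as a mismatch between the enrolment rule, the yield used for the sample size, and the denominators of the specificity and accuracy changes. The plan's arithmetic is right on its own premise; the premise does not cover all the patients it enrols.

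The effect on power is modest: from about 93% to 91, 87 and 83% at assumed shares of 10, 20 and 30%. The effect on interpretation is larger. At those shares, known mimics would be about 22, 38 and 52% of the patients on whom the specificity change is estimated, and the direction of the distortion is open.

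This rests on three assumptions: that known mimics sit inside the 410, which the totals suggest but do not prove; that they add no ALS cases; and that the 60% yield holds in the remaining presenters. The power figures also assume a one-sided test.

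**What to change.** Define the primary analysis set by diagnostic status at entry: patients with no established mimic diagnosis before the initial study evaluation. Count only these toward 405/410, and estimate the primary changes in sensitivity, specificity and accuracy in them. Restricting the set to inclusion route (a) would not achieve this, because (a) lists presenting features and a patient with a known mimic can meet it too.

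Report known LMN and known UMN mimics as two separate groups, outside (c − g)/n, for the second question in Study outline. Give them their own planned number.

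If 410 stays the total including known mimics, state how many are planned and restate the expected ALS cases, the figure of about 160 non-ALS patients and the power for that number.

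The cost depends on the choice. Keeping 410 as the total needs only revised wording in Study subjects, Statistical analysis and Sample size justification, with a somewhat less favourable stated case count and power. Enrolling known mimics on top raises Aim 2 to at least 405 + k and the study total above 650 once k exceeds 5.

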### Measurement of IMC

IMC will be calculated from surface EMG measurements of co-activated muscle pairs. The muscle pair tested in the upper extremity consists of the biceps and brachioradialis [11]; two muscle pairs will be evaluated in the lower limbs: tibialis anterior (TA) and extensor digitorum brevis (EDB), and gastrocnemius lateralis (GL) and gastrocnemius medialis (GM). When testing the upper extremity, the subject performs an antigravity “hold” task in which the forearm is held parallel to the ground and the upper arm is perpendicular to the ground. For assessment of the TA and EDB pair, the subject dorsiflexes the ankle and extends the toes at the same time. For assessment of the GL/GM pair, the subject will be seated with the foot flat on the floor then the heel will be elevated. Each position will be held for 30 seconds at a time, with three repetitions separated by ∼30-second rest blocks.

Surface EMG will be recorded using a sample electrode over the muscle belly and a reference electrode. In preliminary experiments the reference electrode was placed 3 cm from the sample electrode; in ongoing experiments this reference position is being compared to a reference placed over a distant bony prominence. Waveforms will be recorded using clinical EMG systems, either Natus (http://neuro.natus.com/) or Cadwell (http://cadwell.com/), which are available at all the research centers. Signals will be sampled digitally at a minimum of 1000 Hz with pre-amplification low-pass filtering at ∼1/3 the sampling frequency to avoid aliasing.

IMC from the paired EMG signals will be calculated over a range of frequencies, using the algorithm previously reported [23]. Scalar metrics will be calculated by averaging IMC between 10 and 30 Hz (IMC-αβ) or 20 and 40 Hz (IMC-βγ). The precision of a coherence measurement is determined by the number of segments used in the calculation. The confidence limit is defined as:

$$CL=1-\alpha^{1/(S-1)}$$

in which α is the desired significance level (0.05), *S* is the number of segments analyzed, and values below the CL are not statistically different from zero (no coherence) [24].

### Determination of IMC normal-abnormal threshold

Because the ALS diagnostic criteria require a binary determination of the presence or absence of UMN dysfunction, we will set a threshold IMC value below which UMN function is considered abnormal. In a preliminary study we measured IMC-βγ in the right arm of 83 neurotypical controls and 123 subjects with an established ALS diagnosis. These preliminary data were collected prior to initiation of the currently described study protocol, under a separately reviewed and approved IRB protocol (University of Chicago IRB15-0237). IMC measurements were made with the same procedure described above for acquiring surface EMG recordings from the arm. Based on the data shown in Fig 1A (S1 Table; these data have not been previously reported) we found that IMC cutoff values between 0.02 and 0.035 had equivalent diagnostic accuracy using a bipolar recording configuration in the arm (Fig 1B). There was an expected reciprocity between sensitivity and specificity at different cutoff values (Fig 1B). Since the study assesses IMC-βγ added to the current Awaji Criteria, it may increase the sensitivity of the criteria, but runs a risk of reducing the specificity. To minimize the risk to specificity, the cutoff value was selected to optimize accuracy and specificity at the expense of some sensitivity. A cutoff value of 0.025 was selected and will be used in the arm study. A separate cutoff value will be determined for the leg based on the exploratory study on these regions. With this cutoff value, arm IMC-βγ, independent of other diagnostic criteria, has a sensitivity of 60% and a specificity of 83% for ALS compared to neurotypical controls. A low arm IMC-βγ gave an odds ratio (OR) of 7.3 for having ALS (95% CI 3.7 to 14.5; p<0.0001), with an area under the receiver operating characteristic curve of 0.78.

**Fig 1 pone.0303053.g001:**
[figure not shown]
Threshold determination of IMC-βγ. A. IMC-βγ values in neurotypical subjects (n = 83) and ALS patients (n = 123). The dashed line is the cutoff threshold of 0.025, below which IMC-βγ is considered abnormal. B. Accuracy, sensitivity and specificity of IMC-βγ in distinguishing neurotypical from ALS patients, as a function of the IMC value used as a cutoff for abnormal. Dashed line shows the cutoff displayed in A. C. ROC curve showing sensitivity and 1-specificity of the IMC test as a function IMC cutoff value. Area under the curve 0.78.

Two preliminary studies will be carried out to confirm the threshold levels. First, measurements of threshold will be made for different reference electrode positions for the arm and leg in the same subjects. The location of the reference electrodes affects the dynamic range of the coherence measurement and might affect the optimal threshold. Characterizing the effect of reference location on dynamic range and cutoff will also provide information on the reproducibility of the test if reference locations vary in clinical practice. Second, an IMC threshold will be identified for IMC measured in the legs.

